### Statistical analysis

Accuracy of AI-enabled cameras: Taking the grading of images done by the experts as the ground truth, we will estimate the accuracy of the AI- enabled cameras (operated by a non- ophthalmic technician) using standard measures such as sensitivity, specificity, and area under the ROC (Receiver Operating Characteristic). Multivariable regression models will be employed to adjust for potential confounders, including age, diabetes duration, baseline visual acuity, and other relevant factors. These models will allow for a more accurate assessment of the relationships between the intervention and key outcomes, such as disease staging at diagnosis, referral rates, and long-term visual outcomes, by accounting for the influence of these confounders. Both linear and logistic regression models will be used, depending on the nature of the outcome variable, to ensure robust and reliable results. Additional statistical tests, such as chi-square tests for categorical outcomes and t-tests or ANOVA for continuous outcomes, will be employed as appropriate.

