### Objectives

The study aims to show that systematic screening leads to earlier detection of diabetic retinopathy (DR) and reduces visual impairment. It will compare the effectiveness of screening at physician clinics versus routine DR care in eye care settings. The screening program, supported by trained non-medical technicians, is AI-enabled and targets over 90% accuracy in appropriate referral of DR and 80% coverage of eligible people with diabetes (PWD).

The secondary objectives of the study are to: 1. Assess the cost-effectiveness of the AI-enabled systematic screening program and referral pathway compared to the current pathway at an eye care clinic. 2. Evaluate patient satisfaction and adherence to follow-up recommendations in the AI-enabled screening program versus the routine care pathway through an effective digital tracking system.

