### Sample size

We calculate the sample size to detect meaningful differences in the disease staging of patients between two arms at their first eye consultation. Based on the historic data from LVPEI, we assume a 50% prevalence of STDR among DR patients in the SOC arm. Also, we assume that the prevalence of STDR in the intervention arm at the time of screening in the diabetes clinic would be much lower (approximately 10%). However, patients in early stages of DR may not comply with the referral and hence the prevalence of STDR among patients who complete their first ophthalmology visit may be higher (approximately 25%). Based on these estimates, to achieve a power of 80% with a Type-I error rate of 5%, we estimate a sample size of 60 patients in each arm. Since the additional intervention required for the study is minimal (a short check-up using a camera), we expect that about 80% of the eligible patients will consent to participate. Thus, we will need 75 patients with DR to be identified in the intervention arm. Further, based on the historic data at the IDEA clinics, we estimate that 20% of all new registering diabetic patients will have DR. Thus, we will plan to register and screen 375 new diabetic patients each at IDEA clinics (intervention) and LVPEI clinics (SOC arm).

To evaluate the AI tool’s diagnostic accuracy with sensitivity and specificity set at 80%, a sample size of 246 DR-positive cases is required for sensitivity analysis, and 246 DR-negative cases for specificity analysis, assuming a 95% confidence level and a margin of error of ±5%.Given the estimated 20% prevalence of diabetic retinopathy (DR) in the screened population, a total of 1230 patients will be screened to ensure adequate representation of both DR-positive and DR-negative cases.

To assess patient satisfaction, a sample size of **316 patients** will be selected from both the AI-enabled and routine eye care pathways, calculated to detect a difference in satisfaction rates (80% vs. 65%) with a **95% confidence level** and a **margin of error of ±5%**. Random sampling will be employed to ensure unbiased selection of participants from each pathway. This method will involve assigning unique identifiers to eligible patients and using a randomization tool to select participants, ensuring the sample is representative of the study population.

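### The stage-at-diagnosis model treats diabetes duration only as a confounder, although under the earlier-detection hypothesis it may also carry part of the effect; neither the model with it nor the model without it is enough alone

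*Protocol article*

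**What the plan says.** The Statistical analysis section plans regression models to "adjust for potential confounders, including age, diabetes duration", visual acuity at baseline and further unnamed factors. It applies these models to the "relationships between the intervention and key outcomes, such as disease staging at diagnosis, referral rates, and long-term visual outcomes", and says that accounting for the covariates makes the assessment of those relationships more accurate. Both linear and logistic models are planned. Chi-square tests for categorical outcomes are planned as well.

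The Objectives section gives the aim: "The study aims to show that systematic screening leads to earlier detection of diabetic retinopathy (DR) and reduces visual impairment". The Study hypothesis section also speaks of earlier detection. The Sample size section sizes the study to "detect meaningful differences in the disease staging of patients between two arms at their first eye consultation", assuming that 50% of retinopathy patients have sight-threatening disease in the standard-of-care arm and about 25% in the intervention arm among those who complete the first ophthalmology visit.

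The article does not say when age and duration are measured, or whether the crude or the adjusted contrast leads for stage.

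**The concern.** For a given patient, being detected earlier means being detected after fewer years of diabetes. If screening works in that way, patients reach the first eye consultation at a shorter duration and, for that reason, at a milder stage. A model that holds duration fixed compares only patients seen after the same number of years, and so removes the part of the benefit that comes from timing.

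The plan gives duration one role, that of a confounder, and describes the adjusted estimate as the better one. A programme that works as hypothesised could then give an adjusted result close to null, which might be taken to mean that screening does not shift stage. Neither Table 1 nor the Process evaluation metrics list duration at first retinopathy diagnosis, so a benefit in timing would not appear elsewhere under that name.

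**Working it through.** **1. The plan's own figure.** Inputs from Sample size: p₁ = 0.50, p₂ = 0.25, power 80%, type I error 5% (taken as two-sided). With pooled p = 0.375:

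n = [1.960·√(2·0.375·0.625) + 0.842·√(0.25 + 0.1875)]² / 0.25² = (1.342 + 0.557)² / 0.0625 ≈ 57.7, so 58 per arm.

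The plan's 60 reproduces, with power 81.6%. This is an unadjusted two-proportion calculation. The crude odds ratio (OR) is (0.25/0.75)/(0.50/0.50) = 0.33.

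**2. Which covariate matters.** Age = age at diabetes diagnosis + duration. Adjusting for age and duration is therefore the same linear model as adjusting for age at diagnosis and duration; what separates it from a model with age at diagnosis alone is duration. In simulation, adjusting for age alone moves the OR only from 0.33 to 0.38–0.44 when the whole effect runs through timing.

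**3. Simulation.** Model: logit P(sight-threatening) = b·(duration − reference) − d·arm, calibrated to 50% v 25%, 60 per arm. The protocol gives no duration figures, so these are assumptions: detection 4–6 years earlier under screening, SD 5 years. Power is the chance of p < 0.05 in favour of screening.

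| Share of effect through timing | Unadjusted power | Adjusted for duration and age: OR | Adjusted: power |
|---|---|---|---|
| All | about 81% | about 1.0 | 2–3% |
| Half | about 81% | about 0.55 | 24–31% |
| A quarter | about 81% | 0.41–0.43 | 44–54% |
| None, duration gap kept | about 81% | about 0.33 | about 70–75% |

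Full mediation implies that each year of duration multiplies the odds of sight-threatening disease by about 1.7 (4-year gap) or 1.26 (6-year gap).

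**4. Sensitivity to the set-up.** If the duration slope is held fixed and the gap shrinks with the share, adjusted power is 30–38% at half and 86–90% at none. Across set-ups, roughly 13–38% at half and 70–90% at none is a fair summary, but not a bound. A 6-year gap with SD 3 gives about 15% at half; a gap halved to 2 years with a slope of 1.73 per year gives about 51%.

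**5. The opposite case.** Keep the 4–6 year gap, but let it arise because the two clinic populations differ, with no programme effect. The data then have the same distribution as in the table's first row. The model with age at diabetes diagnosis in place of duration declares benefit in 81–82% of runs, and the duration-adjusted model in 2–3%. The first figure is power in one world and a false-positive rate in the other, and the stage data cannot tell the two apart.

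**6. Symptom-driven presentation.** If standard-of-care patients come because of symptoms, the effect survives adjustment: crude OR 0.36, adjusted 0.36; with added delay, 0.33 becomes 0.45.

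**The case against.** The strongest reply is that this is a non-randomised comparison of diabetes-clinic with tertiary eye-clinic patients, in which duration is an obvious case-mix confounder. The Sampling section itself names selection bias and differential access. The intervention arm takes newly registering patients with no earlier fundus examination, so duration may be largely set before the camera is used. All of this stands, and step 5 shows its size. A reader might infer that duration should simply be replaced in the lead model; the documents do not support that, because it exchanges a possible false null for a possible false benefit.

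Further points also stand. Measurement at detection is an inference, though a natural one, since stage is compared at the first eye consultation. Nothing makes the adjusted model primary, and an unadjusted test is also planned; that choice may sit in a fuller plan. Self-walk-ins and referrals in the standard-of-care arm fit symptom-driven presentation, where little is lost. The duration inputs are assumed.

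What the reply does not remove is that the text assigns duration a single role and calls the adjusted result more accurate, while the study's own hypothesis gives duration a second role.

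**Conclusion.** The point holds as a matter of interpretation. Under the study's hypothesis, adjustment for duration can pull the stage estimate toward no effect, at the extreme from an OR of 0.33 to about 1.0 and from about 81% power to about 3%. That extreme needs the whole effect to run through timing. The figures rest on an assumed gap of 4–6 years and SD of 5 years, and illustrate a mechanism rather than forecast a result.

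Three stronger readings do not follow. The plan is not bound to return a null: if none of the effect runs through timing, power is about 70–90%. Age is not an equal culprit; duration does most of the attenuating. Nor is stage the only between-arm comparison that is sized, since the Sample size section also sizes patient satisfaction between the pathways (80% v 65%). A null from the duration-adjusted model alone would not show that detection was no earlier, and a benefit from the model without duration alone would not show that it was.

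**What to change.** Amend the Statistical analysis section as follows.

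- Keep the duration-adjusted stage model and label it as stage at equal diabetes duration.
- Report beside it a stage model adjusted only for factors fixed before detection, for example age at diabetes diagnosis (age minus duration).
- Report diabetes duration at first retinopathy diagnosis by arm.
- State in advance that a null in the duration-adjusted model alone will not be read as no earlier detection, and that a benefit in the other model alone will not be read as proof of it.

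The cost is wording and a little analysis; age and duration are already planned covariates. The downside is two estimates to interpret. Case-mix differences in duration also remain in the model without duration and in the by-arm comparison of duration, so the report should say so.

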## Methods and analysis

### Study design

We will conduct a prospective cohort study involving a comparison between two patient groups: (i) intervention cohort: patients screened at the diabetes clinics using AI and trained nonmedical technicians and referred to the eye clinic as per the proposed pathway, and (ii) standard-of-care (SOC) cohort: patients who arrive at the ophthalmology clinic as per current practice - either self-walk-ins or referrals from other healthcare providers. Fig 1 shows SPIRIT template for clinical trial.

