### Selection of participants

The inclusion criteria for this study in the intervention arm are People with Diabetes (PWD) who visit the diabetes clinics who have never had a fundus examination or fundus photo screening IDEA clinics (Diabetes clinics)/LVPEI(Eye clinics). The referral source will be captured as self-reported, physician, LVPEI network, or ophthalmologist in the standard of care arm -LVPEI eye clinic pathway.

The exclusion criteria for the study are designed to omit individuals with previously diagnosed Diabetic Retinopathy (DR) at the time of presentation to diabetes clinics during the study period. Although we will not include the images of these patients in the study analysis, we will offer appropriate care for their DR at the eye clinic. Additionally, we will seek consent from all eligible participants before they are enrolled in the study and subjected to study protocol. Participants enrolled in the project will be between 18 and 90 years of age.

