**Fig 3 pone.0324382.g003:**
[figure not shown]
Study flow chart.

We will invite eligible patients for screening through a call and recall system. Visual acuity in both eyes will be recorded using a tablet with a web-based vision checking application (Peek Vision). Non-mydriatic fundus photography of both eyes will be performed using AI-integrated retinal cameras (Forus, 3 Nethra Classic HD with AI Integration in two facilities, and Remidio, Fundus on Phone with AI integration, in two facilities). These AI tools have undergone internal validation and published by the company prior to its integration into the cameras [30,31]. Our project, we will be conducting a real-world validation to assess the performance and effectiveness of this AI tool in practical clinical settings.

Diabetic retinopathy grading will be conducted as per International Clinical Diabetic Retinopathy severity scale [32]. Sight-threatening diabetic retinopathy (DR) is defined as severe non-proliferative diabetic retinopathy (NPDR), proliferative diabetic retinopathy (PDR), and moderate to severe diabetic macular edema (DME). The referral criteria include any patient with DR, visual acuity less than 20/60, any other retinal pathology requiring referral, or ungradable retinal images, or any combination of these factors.

In the AI-enabled screening process for Diabetic Retinopathy (DR) using fundus images, if no signs of DR are detected by the AI, the patient will receive a label of “no DR diagnosis” at the initial stage. However, if DR is indicated, a trained technician at the Idea Clinic will manually review the images to confirm or rule out DR, and the result will be communicated to the patient by the physician. Simultaneously, all images will undergo further manual grading at the Central Image Reading Center at LVPEI for quality assurance. If this manual grading results in a change in diagnosis, the updated result will be shared with the patient within a week since their initial screening.

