### Program outcomes

The program’s outcomes will be evaluated through metrics such as screening uptake rate, sensitivity, and specificity of AI versus manual system, ROC Curve for AI Diagnostic Accuracy for diagnosis of DR, referral rate, cost-effectiveness, patient and provider satisfaction, follow-up rates, and long-term outcomes. These outcomes will help determine the program’s impact on patient health and healthcare costs. Due to the formatting constraints of the CTRI registry, certain fields were filled in a specific way, which might lead to minor discrepancies between the reported outcomes in the manuscript and the CTRI registry. (Table 1 shows the outcome measurement indicators for the project.).

**Table 1 pone.0324382.t001:** Outcome measurement indicators: SMART DROP project.

Outcome	Definition	Numerator	Denominator
Screening uptake rate	Proportion of eligible patients who underwent DR screening out of the total eligible population.	Number of eligible patients who underwent DR screening	Total number of eligible patients in the population
Sensitivity of AI system	Proportion of true positive DR cases correctly identified by the AI system.	Number of true positive DR cases identified by the AI system	Total number of true DR cases confirmed by manual grading
Specificity of AI system	Proportion of true negative cases correctly identified by the AI system.	Number of true negative DR cases identified by the AI system	Total number of non-DR cases confirmed by manual grading
ROC curve for AI diagnostic accuracy	A graphical plot showing the diagnostic ability of the AI system by plotting true positive rate (sensitivity) against false positive rate (1-specificity).	True positive rate (sensitivity)	False positive rate (1-specificity)
Referral rate	Proportion of screened patients referred for further examination or treatment.	Number of patients referred for further examination or treatment	Total number of patients referred
Cost effectiveness	Ratio of the total costs associated with the screening program to the health outcomes achieved, typically measured as cost per quality-adjusted life year (QALY).	Total costs of the screening program	Total health outcomes achieved (e.g., QALYs gained, cases of blindness prevented)
Patient satisfaction	Proportion of patients reporting satisfaction with the DR screening process and outcomes.	Number of patients reporting satisfaction	Total number of patients who completed the satisfaction survey

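### Referral rate is listed as an outcome of the intervention, but it has no defined counterpart in the standard-of-care arm, so the planned between-arm model has no interpretable effect to estimate

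*Protocol article*

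**What the plan says.** The protocol article's Statistical analysis section says multivariable models will estimate "relationships between the intervention and key outcomes, such as disease staging at diagnosis, referral rates, and long-term visual outcomes", adjusted for age, diabetes duration, baseline visual acuity and other factors. On the model it says "Both linear and logistic regression models will be used, depending on the nature of the outcome variable". Chi-square tests are added for categorical outcomes.

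Study design defines the two arms. The intervention cohort is "patients screened at the diabetes clinics using AI and trained nonmedical technicians and referred to the eye clinic as per the proposed pathway". The SOC cohort is "patients who arrive at the ophthalmology clinic as per current practice - either self-walk-ins or referrals from other healthcare providers".

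In the intervention arm, referral follows a rule given under Study procedures: "The referral criteria include any patient with DR, visual acuity less than 20/60, any other retinal pathology requiring referral, or ungradable retinal images". For the SOC arm, Selection of participants describes an inbound variable only: "The referral source will be captured as self-reported, physician, LVPEI network, or ophthalmologist in the standard of care arm".

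Table 1 (Program outcomes) defines referral rate as "Proportion of screened patients referred for further examination or treatment". It prints the denominator as "Total number of patients referred", which does not match that definition. No SOC version is given.

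**The concern.** An arm effect on an outcome needs the same event, at risk of occurring in both arms after entry. Here the intervention event is being sent from a diabetes clinic to the eye clinic. An SOC patient joins the study by already being at the eye clinic. What the article describes for that patient is the route of arrival, which is an entry characteristic and not an outcome.

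Adjusting for age, duration and acuity cannot repair this, because the problem is what is being counted and not an imbalance in who is counted. The direction is also unhelpful: more ungradable images or more false-positive screens would raise the intervention arm's rate and could be read as a larger programme effect. The Abstract names referral rates as a success metric and the Conclusion expects referral-pathway evidence to inform policy, so the estimate is likely to be quoted.

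**Working it through.** **Inputs from the document (Sample size).** 375 patients registered and screened in each arm; 20% of new registrants estimated to have DR; STDR 50% (SOC) against 25% (intervention) at the first eye visit; 80% power; 5% type I error (two-sided assumed). No referral rate is stated for either arm.

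**Inferred input.** Any DR triggers referral, so an intervention rate of about 20%, or 0.20 × 375 = 75 patients, is a working floor. Acuity, other pathology and ungradable images would add to it.

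**The plan's own figure.** n = [1.96√(2 × 0.375 × 0.625) + 0.842√(0.5 × 0.5 + 0.25 × 0.75)]² / 0.25² = 58 per arm, which agrees with the stated 60 (power at 60 is 81.6%). Then 60/0.8 = 75 and 75/0.2 = 375. These figures concern disease staging and do not depend on referral rate.

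**Reading 1: screening referral to the eye clinic. SOC is 0/375 by construction.**
- At 75/375 against 0/375, chi-square = 750 × (75 × 375)² / (375 × 375 × 75 × 675) = 83.3, p about 7 × 10⁻²⁰. Fisher p = 8.6 × 10⁻²⁵.
- Fisher's test reaches p < 0.05 from 6 intervention referrals upward (Pearson chi-square from 4). The Fisher rejection probability is P(X ≥ 6) with X ~ Binomial(375, p):

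| Intervention referral rate | P(reject) |
|---|---|
| 1% | 18% |
| 2% | 76% |
| 3% | 97% |
| 5% | 99.99% |
| 20% | about 100% |

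- The logistic model on the same data shows quasi-complete separation. One fitting routine stops with a singular matrix. Another returns a coefficient of 25.2 with a standard error of about 18,390 and Wald p = 0.999.

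So one dataset gives p near 10⁻²⁰ or p = 0.999, depending on which method from the Statistical analysis section is used.

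**Reading 2: the SOC rate is the share arriving by referral, or the share referred in-house for treatment.** The rate is free and not stated. Assumed range 10% to 50%, against 20% in the intervention arm, two-proportion normal approximation, 375 per arm:

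| Assumed SOC rate | P(reject) |
|---|---|
| 10% | 97% |
| 15% | 44% |
| 20% | 5% |
| 25% | 37% |
| 30% | 89% |
| 50% | about 100% |

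The test is well behaved here, but the arms count different things: a screening result against a route of arrival, or referral into the eye clinic against referral within it.

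**Reading 3: the denominator as printed in Table 1.** Patients referred divided by patients referred is 100% in both arms, so there is no contrast.

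**The case against.** The strongest reply is that the SOC rate is not shown to be zero. Sample size says that patients at the eye institute are also registered and screened. Table 1 counts referral for treatment as well as for examination. Process evaluation has a timely referral rate for management of STDR that is not limited to one arm. All of this stands, and it means the SOC rate is undefined rather than fixed.

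A reader might therefore go too far in inferring that the design guarantees a significant result whatever the programme does. The document does not support that. It holds only if the SOC rate is 0% (or, by the same argument, 100%), only for a chi-square, Fisher or similar test, and only with more than a few referrals. The Wald test from the logistic model would not reject, and under the printed denominator nothing can.

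It can also be said that the list of outcomes is illustrative, that referral rate is not the powered outcome, and that arm-specific definitions are often left to an analysis plan. The first two are correct and limit the weight of the point. The third does not remove it: the article itself names the outcome, the contrast and the models, and the referral rate it defines does not fit that contrast.

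**Conclusion.** The point holds as one of definition and interpretability. None of the readings that the text allows gives an arm coefficient for referral rate that measures what the programme did. Under the screening-referral reading, the result is decided by the design at the planned numbers (chi-square 83.3) or cannot be estimated (logistic). Under the other readings, rejection can lie anywhere from 5% to about 100%, according to an SOC rate that the document does not give, and the events compared are different.

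This rests on three assumptions: the 20% intervention rate is inferred from the DR estimate; the 10% to 50% SOC range is assumed; tests are two-sided at 5%. The staging comparison and its 60, 75 and 375 patients are unaffected. The change is worth making before analysis because referral rate is a named success metric and the correction is small.

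**What to change.** In Statistical analysis, take referral rates out of the outcomes modelled by arm. Report the referral rate for the intervention arm only, with patients screened as the denominator (correcting Table 1) and a 95% CI; at 75/375 the Wilson interval would be 16.3% to 24.3%. Split it by reason (DR, acuity, other pathology, ungradable image) and by whether the reading centre confirmed the reason. Report SOC referral source as a baseline characteristic.

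If an arm comparison is wanted, first define an event that both arms can have after the first eye consultation, counted from the same starting point. Candidates already in Process evaluation are timely referral for management and treatment uptake, each among patients with STDR.

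The cost is a sentence of analysis wording and one table cell, with no new data. The downside is one fewer between-arm outcome.
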